### Participant Retention

Inviters who choose to extend physical invitation cards to their network contacts will be recontacted by phone after 30 days and asked whether they distributed these cards to their contacts. For all other inviters, study activities will end after the initial visit.

### Study Timeline

Details of the intervention will be finalized after formative qualitative work, including focus group discussions and in-depth interviews with HCT clients, CTC patients, and providers. Focus group discussions and in-depth interviews will explore ethical considerations and elucidate key client-side characteristics of CONSORT, including refining appropriate SMS text message content for invitees, defining parameters for the timing of invitation messages, and exploring the feasibility of incentives for inviters and invitees. Before the implementation of the RCT, the intervention will be pilot-tested with 50 adult HCT clients and 50 adult CTC patients. Formative work and pilot testing are expected to last 2 years.

Following formative work and a successful pilot test, the RCT is planned to commence in year 3 of this study. Enrollment in the RCT will continue until the target numbers of 400 HCT inviters and 200 CTC inviters have been reached. Assessments of invitation card distribution and HIV testing uptake will continue until 30 days after the last CONSORT invitation was sent through mParis and the last invitation card was issued.

### Statistical Analysis

#### Analysis of the Primary Outcome

Efficacy will be analyzed descriptively by comparing, between the 2 study arms, the number of invitees testing for HIV within 1 month per 100 inviters (Figure 3). Analytically, efficacy will be modeled at the level of the inviter, using a zero-inflated negative binomial model, with the number of invitees returning for testing as the dependent variable. The primary explanatory variable will be a binary indicator variable for the study arm. Covariates will characterize variation in invitees’ testing uptake with inviters’ sociodemographic and network characteristics, HIV risk, and stigma.

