**Figure 2 figure2:**
[figure not shown]
The design of the 2-arm randomized controlled trial (RCT). This RCT with 600 adult inviters will be conducted in Moshi, Tanzania. The primary outcome of interest is the uptake of HIV testing among invitees, defined as the number of invitees testing for HIV within 30 days of enrollment of the inviter per 100 inviters. While not all process elements can be observed, the RCT results yield an unbiased estimate of the efficacy of the Confidential Social Network Referrals for HIV Testing (CONSORT) for the primary outcome: inducing additional persons to test for HIV relative to physical invitation cards alone.

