#### Assignment to Study Arms

Participant IDs will be randomly assigned to either arm 1 or arm 2 using a random number generator. The random assignment is expected to result in approximately equal numbers of participants in each study arm.

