#### Analytic Considerations

The analysis of the primary outcome will be stratified by cohort (HCT inviters: n=400; CTC inviters: n=200); generalized Hausman tests will evaluate whether the data can be pooled.

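### The arm coefficient of the zero-inflated primary model need not be the effect on testers per 100 inviters; a contrast on that scale should be named as primary

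*Protocol article*

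**What the plan says.** The Figure 2 legend gives the primary outcome as uptake of testing among invitees, "defined as the number of invitees testing for HIV within 30 days of enrollment of the inviter per 100 inviters". The Figure 3 legend uses the same scale.

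Analysis of the Primary Outcome then has two steps. The first is descriptive: "Efficacy will be analyzed descriptively by comparing, between the 2 study arms, the number of invitees testing for HIV within 1 month per 100 inviters". No test or interval is attached to it. The second is inferential, with the inviter as the unit, and is to be done "using a zero-inflated negative binomial model, with the number of invitees returning for testing as the dependent variable". Treatment enters through a single term: "The primary explanatory variable will be a binary indicator variable for the study arm". Covariates are to reflect "inviters’ sociodemographic and network characteristics, HIV risk, and stigma". The section does not say whether arm enters the count part, the zero part or both, and it names no contrast that returns the fit to testers per 100 inviters.

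Analytic Considerations stratifies this analysis by cohort (400 HCT and 200 CTC inviters). Statistical Power works with 20 to 100 arm 2 testers and says that the control-arm rate is not known.

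**The concern.** A zero-inflated negative binomial has two linear predictors: one for belonging to a group that can only give zero, and one for the count in the rest. The primary outcome is neither. It is the mean over everyone. A plan that makes this model its only inferential analysis, with one arm indicator and no named marginal contrast, leaves open that the reported effect belongs to a latent subgroup, or is a biased version of the ratio the trial wants. The headline estimate could then disagree with the descriptive comparison beside it.

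The route by which CONSORT might act makes this more than a formality. Cards in arm 2 depend on the inviter handing them over, and Phone-Based Follow-Up Survey checks this by self-report. CONSORT messages go out from mParis without further action by the inviter. An effect partly on whether an inviter yields any tester is therefore plausible, though the article does not state it. A second worry is stability: few testers, several families of covariates and a 200-inviter cohort are demanding for a two-part model. A failed fit would force a change of primary model in a trial where staff are not blinded.

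**Working it through.** **Inputs.** 600 inviters (Figure 2 legend) in "approximately equal numbers of participants in each study arm" gives about 300 per arm, or about 100 per arm in the CTC cohort. Arm 2 testers of 20 to 100 come from Statistical Power. That is 20/300 = 0.07 to 100/300 = 0.33 per inviter, so at most 7% to 33% of arm 2 inviters can have a non-zero count. The article gives no figure computed under the zero-inflated model. Its detectable differences treat the total as Poisson, so there is nothing to reproduce here.

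**Step 1: what the coefficients mean.** Let π be the structural-zero share and μ the count mean in the rest. The overall mean is (1 − π)μ, and the ratio of overall means is

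R = [(1 − π₁)/(1 − π₂)] × (μ₁/μ₂).

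The count-part coefficient is μ₁/μ₂. It equals R only if π₁ = π₂.

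Example: π falls from 0.80 in arm 2 to 0.65 in arm 1, with μ = 1 in both.
- Overall means are 0.20 and 0.35, so R = 0.35/0.20 = 1.75, a difference of 15 testers per 100 inviters.
- The count-part ratio is 1.00.
- The zero-part odds ratio is (0.65/0.35)/(0.80/0.20) = 0.46.
- Neither of the last two is 1.75.

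**Step 2: simulated size.** Assumptions: 300 per arm, alpha 0.05, no covariates and 150 replicates (Monte Carlo error about 4 points). Zero-part data have a mean of 1 tester per active inviter, count-part data an active share of 0.4, and plain negative binomial data size 0.5. ZI is the zero-inflated model; the comparator is the ratio of arm means with robust variance.

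| Effect acts on | Testers, arm 2 vs 1 | True ratio | ZI, arm in count part only: median ratio | ZI, arm in both parts: median count-part ratio | Power, ZI count part only | Power, robust ratio of means |
|---|---|---|---|---|---|---|
| zeros | 20 vs 40 | 2.00 | 1.68 | 0.97 | 23% | 41% |
| zeros | 60 vs 100 | 1.67 | 1.48 | 1.00 | 38% | 63% |
| zeros | 100 vs 150 | 1.50 | 1.42 | 1.02 | 49% | 76% |
| count | 60 vs 100 | 1.67 | 1.66 | 1.75 | 65% | 77% |
| plain negative binomial | 60 vs 100 | 1.67 | 1.66 | 1.63 | 71% | 70% |

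A separate run with a true ratio of 1.75 acting through zeros gave a median of about 1.53 with arm in the count part only, and 0.96 to 1.03 for the count coefficient with arm in both parts.

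**Step 3: what can be recovered.** In the setting of the Step 1 example (assumed dispersion 0.5, arm in both parts, 200 replicates), the marginal mean ratio predicted from the zero-inflated fit matched the raw ratio of arm means to about four decimals (median 1.718 for both). A joint 2-df likelihood-ratio test of arm had 70% power against 62% for the robust comparison of means, with null rejection of 4.5% to 6.5%. Other runs with the effect on zeros gave 59% to 78% for the joint test against 44% to 73%.

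**Step 4: fit.** With arm and 4 assumed covariates (40 replicates), non-convergence or unusable standard errors occurred in 88–97% of fits at 20 vs 27 testers, 62–68% at 60 vs 73 and 45–53% at 100 vs 116. At 100 inviters per arm with 20 vs 27 testers the figure was 85–88%. With arm and 6 assumed covariates in both parts under the null, fits failed in 35 of 60 runs (58%) with 100 arm 2 testers, and in 52 of 60 (87%) in a 200-inviter cohort with 33.

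**The case against.** The case for the plan is substantial. A zero-inflated negative binomial is a recognised model for counts with many zeros. A reader might infer that it cannot estimate the primary outcome at all; that does not follow. Step 3 shows that the overall means are recoverable, and with equal zero shares the count-part coefficient is the right ratio.

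A reader might also take a near-null count coefficient with arm in both parts as proof that the trial would miss a real effect. When the whole effect is placed on the zeros, that coefficient is truly null, so failing to reject it is correct behaviour and not lost power. A joint test does at least as well as the comparison of means.

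The mechanism is inferred. The article lets arm 1 inviters invite any contact, which allows an effect on the count, and its Discussion says that a confidential message is probably less motivating than personal communication. The failure rates rest on invented covariate numbers and on particular software. Boundary fits with π near zero simply collapse to an ordinary negative binomial with a usable coefficient.

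Lastly, the covariate list, the placement of arm and a convergence fallback are ordinary SAP content, and no SAP is shown. All of this stands. What it does not remove is that the article itself fixes a two-part model with an arm indicator as the only inferential analysis of an outcome defined on the overall mean. One natural reading, arm in the count part only, is biased towards no effect whenever CONSORT lowers the structural-zero share.

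**Conclusion.** The point holds in a limited form. The stated model's arm coefficient need not be the effect on testers per 100 inviters. With arm in the count part only and an effect through zeros, the estimate was about 1.5 for a true 1.67 to 1.75, and power at 60 vs 100 testers was 38% against 63% for a direct comparison of means. With arm in both parts, neither coefficient is the effect, but nothing is lost if the marginal means are predicted and arm is tested jointly. The article plans neither.

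Unstable fitting is a real risk at the tester counts assumed in Statistical Power, but the rates are illustrative. Those counts are not expected values, because the control rate is unknown.

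The results rest on the assumed alpha, dispersion, zero shares and covariate numbers given in the working. The documents do not support calling the model invalid or the trial unable to detect its effect. This is a worthwhile and cheap improvement, not an error that must be corrected before the trial can be interpreted.

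**What to change.** In Analysis of the Primary Outcome, name the primary contrast as the ratio of mean testers per inviter between arms, together with the difference per 100 inviters, each with a 95% CI. Estimate it from a log-link Poisson or negative binomial model with robust (sandwich) standard errors, including arm, cohort and a short prespecified list of baseline covariates. Keep the zero-inflated negative binomial as a secondary analysis of mechanism, summarised by its marginal mean ratio.

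The cost is wording only; no data collection or sample size changes. There are two small downsides. The split between any tester and how many testers becomes secondary. If the effect is purely on zeros, some power may be lost relative to a joint test in the zero-inflated model (62% against 70% in one of the runs above).

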**Figure 3 figure3:**
[figure not shown]
Visual representation of the estimated effect of Confidential Social Network Referrals for HIV Testing (CONSORT) on the primary outcome: number of invitees testing for HIV within 30 days per 100 inviters (hypothetical). The 2-arm randomized controlled trial with 600 adult inviters will be conducted in Moshi, Tanzania.

#### Analyses of Secondary Outcomes

##### Acceptability Among Inviters

Logistic regression will be used to model inviters’ decisions to send at least 1 CONSORT invitation. Zero-inflated negative binomial models will model the number of invitations sent as a function of the covariates described above.

##### New HIV Diagnoses

Differences between study arms in the number of new HIV diagnoses among invitees, per 100 inviters, will be analyzed descriptively using a Fisher exact test.

##### HIV Risk Among Invitees

Differences in invitees’ sociodemographic and risk characteristics between study arms will be assessed descriptively using 2-tailed Student *t* tests and chi-square statistics.

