### The CONSORT Intervention

The CONSORT process is shown in Figure 1. A consented inviter completes an HIV risk assessment and a survey of their social and sexual network contacts. Next, the inviter selects invitation messages from a menu of options to send to any of their network contacts who they think could benefit from HIV testing. Invitee phone numbers and SMS text messages are transferred securely to mParis. mParis autonomously sends the invitation SMS text message with a unique referral code to each invitee phone number. Invitees presenting for HIV testing with a referral code (invitee testers) will be offered the opportunity to become inviters (Figure 1).

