#### Design of the RCT

The design of the 2-arm RCT is shown in Figure 2. Arm 1 participants will be offered to extend CONSORT invitations or physical invitation cards to any of their network contacts. Arm 2 participants will be offered physical invitation cards alone. Arm 1 represents the intervention arm; Arm 2 represents the active control arm.

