#### Assessment of Secondary Outcomes

The acceptability of CONSORT among inviters will be described by the percentage of inviters extending at least 1 CONSORT invitation and the average number of CONSORT invitees per inviter. This outcome is assessed only for arm 1 participants.

For invitee testers, basic sociodemographic and risk characteristics (age, gender, marital status, pregnancy status, and previous testing), as well as their HIV test result, will be abstracted in aggregate form from administrative data collected for reports to Tanzania’s National AIDS Control Programme (NACP). Clients testing positive for HIV will be linked to care at a local CTC, following NACP guidelines [16]. Invitee testers consenting to become inviters will complete the same enrollment survey as their inviters, which includes a comprehensive HIV risk assessment.

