## Discussion

### Overview

This study will evaluate the acceptability and efficacy of automated, confidential SMS text message–based HIV testing invitations as a means of nudging individuals to test for HIV. If testing rates are higher in arm 1 invitees than arm 2 invitees, the results will support our hypothesis that an automated, confidential referral system is acceptable to both index participants (inviters) and referrals (invitees) and is effective for increasing uptake of HIV testing. If CONSORT is shown to be acceptable and effective, then confidential, digital, chain-referral methods could be used to improve the reach and cost-effectiveness of HIV testing efforts.

CONSORT’s potential is based on 3 key premises.

The first premise is that testing network contacts of persons living with HIV and those testing for HIV is an effective means for HIV case-finding. Identifying, tracing, and testing sexual contacts of persons with a sexually transmitted infection has been an essential component of public health sexually transmitted infection management for decades. Assisted HIV partner notification, by which health care workers elicit information about an index case's sexual partners and contact partners to request HIV testing, has been shown to be effective for increasing testing uptake and identifying new HIV infections [26-36]. A meta-analysis of 3 individual randomized trials [33-35] found that assisted partner notification, compared with passive referral, resulted in a 1.5-fold increase in HIV testing uptake. Moreover, the proportion of HIV-positive partners identified was 1.5 times higher with this approach [37]. Previous research also suggests that persons presenting for HIV testing have higher rates of HIV infection and higher rates of HIV risk behaviors than the general population [38,39]. Owing to similarities between members of social networks, a property known as homophily, referrals of HCT and CTC clients are, thus, also more likely to be infected with HIV than the general population. CONSORT*,* therefore, is well positioned to reach populations with an above-average risk of HIV infection and nudge them to test for HIV.

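### The tests named for invitee characteristics ignore clustering by inviter, and the Fisher test for new diagnoses has no defined binary unit; data aggregated only by arm would block the remedy

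*Protocol article*

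**What the plan says.** All references are to the protocol article.

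- **Unit of randomisation** (Assignment to Study Arms): "Participant IDs will be randomly assigned to either arm 1 or arm 2 using a random number generator". The IDs are those of inviters, and the section expects "approximately equal numbers of participants in each study arm".
- **Several invitees per inviter** (Design of the RCT): arm 1 inviters may "extend CONSORT invitations or physical invitation cards to any of their network contacts". Arm 2 inviters are offered cards alone.
- **Invitee characteristics** (HIV Risk Among Invitees): sociodemographic and "risk characteristics between study arms will be assessed descriptively using 2-tailed Student" t tests and chi-square statistics. No allowance for shared inviters is mentioned.
- **New diagnoses** (New HIV Diagnoses): the between-arm difference in the number of diagnoses among invitees, "per 100 inviters, will be analyzed descriptively using a Fisher exact test".
- **Form of the data** (Assessment of Secondary Outcomes): basic characteristics and test results of invitee testers "will be abstracted in aggregate form from administrative data". The level of aggregation is not given. Testers who consent to become inviters also complete the full individual survey.
- **Similarity within networks** (Discussion, Overview): "Owing to similarities between members of social networks, a property known as homophily" is the ground for expecting referrals of testing and care clients to carry above-average HIV risk.

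By contrast, the primary outcome (Analysis of the Primary Outcome) is modelled as a count per inviter.

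**The concern.** Invitees are nested within randomised inviters, and the protocol's own rationale is that people in one network resemble each other. A t or chi-square test on individual invitees counts two testers from the same inviter as two independent pieces of information. If they are alike, the standard error is too small, and so is the p-value.

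The new-diagnoses outcome has a different problem. It is a count to which one inviter can contribute more than one event, whereas Fisher's test compares proportions of independent units that are each a yes or a no. Three readings are possible: diagnoses over inviters, diagnoses over testers, or inviters with at least one diagnosis. They answer different questions. With testers as denominator the test is about positivity among those who presented, a subset formed after randomisation, and no longer about diagnoses per 100 inviters.

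At stake is the stated precision on who CONSORT reaches and how many new cases it finds. The data format has to be settled before abstraction starts.

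**Working it through.** The protocol states no figure for these tests, so there is none to reproduce.

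**Inputs from the protocol.** 600 inviters in about equal arms, so about 300 per arm. Statistical Power considers 20, 40, 60, 80 or 100 testers in arm 2, so the mean number of testers per inviter is μ = 20/300 = 0.07 up to 100/300 = 0.33.

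**Assumptions.** The same number of testers in each arm; two-sided 5% level; intra-inviter correlation (ICC) 0.05 to 0.30; testers per inviter negative binomial with dispersion k from 0.1 (concentrated in few inviters) to 1.

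**Formulas.**
- Tester-weighted cluster size: m = E[n²]/E[n] = 1 + μ(1 + 1/k), where n is testers per inviter
- Design effect: DE = 1 + (m − 1) × ICC
- True type I error: 2 × [1 − Φ(1.96/√DE)]

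**Worked extremes.**
- 20 testers, k = 1, ICC 0.05: m = 1 + 0.0667 × 2 = 1.133; DE = 1 + 0.133 × 0.05 = 1.007; error 5.1%.
- 100 testers, k = 0.1, ICC 0.30: m = 1 + 0.333 × 11 = 4.667; DE = 1 + 3.667 × 0.30 = 2.10; error 17.6%.

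| Testers per arm | DE, lowest to highest | True error of a nominal 5% test |
|---|---|---|
| 20 | 1.01 to 1.22 | 5.1% to 7.6% |
| 60 | 1.02 to 1.66 | 5.2% to 12.8% |
| 100 | 1.03 to 2.10 | 5.4% to 17.6% |

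**Simulation check** (chi-square on testers, 2,000 runs, outcome prevalence 50%, no true difference; Monte Carlo standard error about 0.5 points at 5%). With k = 0.25 and ICC 0.1: 4.9% at 20 testers and 5.8% at 100. With k = 0.1 and ICC 0.3: 16.2% at 100. These agree broadly with the formula.

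**Fisher's test, illustrative 8 versus 2 new diagnoses.**
- Over 300 inviters per arm (8/300 v 2/300): p = 0.106.
- Over testers, taking 60 v 40 (8/60 v 2/40): p = 0.308.
- Exact comparison of the two counts (8 of 10 events): p = 0.109.

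**Simulated type I error of Fisher's test** (300 inviters per arm, 5% HIV positivity among testers, assumed).

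| Reading | k = 0.25, ICC 0.2; 20 / 60 / 100 testers | k = 0.1, ICC 0.3; 100 testers |
|---|---|---|
| Over testers | 0.4% / 3.7% / 4.9% | 11.5% |
| Diagnoses over inviters | 0% / 1.9% / 4.0% | 10.5% |
| Inviters with at least one diagnosis | 0% / 0.9% / 1.5% | 1.4% |

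Only the last reading gives one yes/no per randomised unit, and it stays below 5% throughout.

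**Not modelled.** The CONSORT Intervention section adds that "Invitees presenting for HIV testing with a referral code (invitee testers) will be offered the opportunity to become inviters". Dependence along referral chains would be a further source of correlation.

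**The case against.** **Size unknown.** The protocol gives no ICC and no distribution of testers. At 0.07 to 0.33 testers per inviter, many may come singly, and inflation may be negligible. This stands: the p-values can be too small, and a reader who infers that they must be goes beyond the documents.

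**Fisher is not generally too liberal.** With rare diagnoses it is often conservative, and over testers the example gives a larger p-value (0.31 against 0.11). This stands too. The fault in that section is the undefined unit, and it would be wrong to infer that its p-values are systematically too small.

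**Clustering could still be handled.** A reader might infer from the aggregate abstraction that correction is impossible, or that a t test could not be computed. The text supports neither. It does not say how far the data are aggregated, and aggregates can carry means and SDs by arm. Assessment of Primary Outcome validates referral codes against those issued, the primary model needs testers per inviter, and testers who enrol give individual data. Adjustment is blocked only if the data are held as arm totals. Those who enrol are, however, a self-selected part of all testers.

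**Secondary, descriptive, and a matter for the full plan.** The Discussion ties support for the hypothesis to testing rates by arm, not to these tests. That lowers the consequence. But the article names specific tests for named secondary outcomes, so this is a stated choice and not an omitted detail.

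**Confidentiality.** Linking HIV results of testers who never consented to research goes beyond aggregate abstraction. It must be reconciled with the separate storage of invitee and inviter information (Ethical Considerations) and with the lack of contacts' consent to giving their numbers (Limitations and Considerations). This stands and shapes the fix.

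**Conclusion.** The point holds in a limited form. The t and chi-square tests assume an independence that the design and the homophily argument contradict. Under the assumed ICC (0.05 to 0.30), dispersion (k 0.1 to 1) and 20 to 100 testers per arm, the true error of a nominal 5% test lies between about 5% and about 18%. The upper end needs both many testers and strong concentration in few inviters.

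For new diagnoses, Fisher's test is applied to a count without a valid binary unit. The result depends on the denominator, and using testers changes the question.

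Arm-level totals would prevent adjustment; finer abstraction would not. The primary analysis is unaffected by this point. The change is worth making because it is specific and the abstraction format must be settled in advance.

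**What to change.** 1. **New diagnoses.** Compare at inviter level: permute arm labels on diagnoses per inviter, or apply Fisher's test to inviters with at least one new diagnosis, and state which. Continue to report diagnoses per 100 inviters. Do not substitute an exact Poisson comparison of counts, which also assumes independent events.
2. **Invitee characteristics.** Use regression or GEE with standard errors clustered on inviter. This corrects the precision; the comparison remains one among those who presented.
3. **Data.** State the level of aggregation. Abstract the same fields by coded inviter ID, or as de-identified records keyed to the referral or card code, instead of by arm total. Keep this consistent with the separate storage described under Ethical Considerations and subject to ethics approval.
4. **Fallback.** If that is not approved, limit the clustered analysis to the surveys of consenting invitee testers and report the aggregate comparisons without p-values.

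**Cost.** The registers and fields are unchanged. The price is handling coded data, an ethics amendment, and slightly wider intervals.
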